### Primary and secondary endpoints

#### Primary endpoint

The primary endpoint will be the frequency of post-interventional pneumothorax and haemothorax. Pneumothorax and haemothorax will be defined as the presence of air or blood in the pleural space, respectively. The rate of pneumothorax and haemothorax will be assessed two hours post-implantation by means of a chest X-ray (in inspiration) by the responsible physician if PSV was performed. In the event that SCD with or without RT is successful, a chest X-ray will be performed only in patients with suspicion or symptoms of pneumothorax or haemothorax (for example dyspnoea), since SCD has no associated risk of these conditions. A copy of the post-operative pneumothorax and/or haemothorax control radiograph will be saved in digital form, using radiological image viewing software (such as Centricity®, GE Healthcare, Buckinghamshire, United Kingdom), or a copy of the original radiograph will be archived. The presence of pneumothorax and haemothorax will be documented in the case report form (CRF). At follow-up visit three on day 30, the study nurse will also ask the patient about further post-operative occurrence of pneumothorax and haemothorax and check the patient’s documents for further diagnostic and treatment procedures in this regard.

#### Secondary endpoints

##### Duration of port implantation procedure

For the open strategy, the time from cutaneous incision to last knot of intracutaneous suture and the time from the patient entering the intervention room until the patient has left, will be measured. For the closed strategy, the time from first intervention on the patient (that is, first sonography, first radiography or first puncture) to the last knot of the intracutaneous suture, and the time from the patient entering the intervention room until the patient has left, will be measured. Both time measurements will be documented in the CRF on the day of intervention by the surgeon or a study nurse.

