#### Intervention group A (open strategy)

Following the infiltration of local anaesthesia in sterile fashion into the skin and subcutaneous layer, a cutaneous incision will be made over the deltopectoral sulcus region to expose the cephalic vein. The cephalic vein will be ligated distally and encircled cranially with an resorbable suture. The vein will be transected ventrally (Figure 2a) and the catheter, flushed with heparinised saline, will be introduced. If simple SCD is not successful, the RT will be used as a second step. Therefore, catheter insertion will be supported by use of a guide wire (Figure 2b, c), vein dilator and peel-away sheath through the cephalic vein (Figure 2d). The guide wire and dilator will be removed, and the catheter easily introduced through the peel-away sheath, which can be removed afterwards (Figure 2e, f).

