**Figure 2 Fig2:**
[figure not shown]
**Photo documentation of the rescue technique. a)** Ventral transection of cephalic vein. **b)** Introduction of a guide wire due to narrow cephalic vein. **c)** Radiograph of intravascular course of the guide wire. **d)** Introduction of vein dilator and peel-away sheath. **e)** Insertion of catheter and removal of peel-away sheath. **f)** Correctly placed catheter in cephalic vein and fixation.

Correct positioning will be controlled via X-ray, fluoroscopy (tip of the catheter in the superior vena cava just at the level of bronchial bifurcation) or intraatrial electrocardiogram. The catheter will be connected to the port chamber. Using the same incision, a subcutaneous pocket will be prepared by blunt preparation on the pectoral fascia. The port chamber will be fixed on the fascia of the pectoral muscle with three single non-absorbable sutures. Wound closure will be performed in accordance with the local standards of the trial centres. Flow for blood withdrawal and infusion will be tested via cutaneous puncture (Huber needle). To complete the procedure, the system will be blocked by means of saline with or without heparin, according to the local standards.

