#### Intervention group B (closed strategy)

Guidance for the puncture by means of sonography, fluoroscopy or the landmark technique is permitted. For fluoroscopy guidance, patients receive a peripheral venous catheter on the side of the planned puncture location to administer the contrast agent and check that the subclavian vein is not obstructed by a thrombosis (roadmap technique). For sonography guidance, a standard ultrasound device can be used to visualise the subclavian vein. The landmark technique uses anatomical landmarks (clavicle, jugular fossa, and so forth) to identify the right position for PSV. Local anaesthesia will be infiltrated in sterile fashion into the skin and periosteum of the clavicle. The location of the puncture will be marked between the proximal and medial third of the clavicle. A skin incision can be performed above the puncture location.

After that, the subclavian vein will be punctured using the Seldinger technique and a guide wire will be introduced. An introducer sheath will be passed over the guide wire into the vein. The guide wire will be removed and the port catheter introduced through the introducer sheath. Correct position will be checked by X-ray, fluoroscopy or intraatrial electrocardiogram. A subcutaneous pocket will be prepared by blunt preparation on the pectoral fascia through the same incision. Alternatively, a second skin incision can be performed and a subcutaneous pocket will then be prepared bluntly on the pectoral fascia. The port chamber will be fixed on the fascia of the pectoral muscle with three single non-absorbable sutures. Wound closure will be performed in accordance with the local standards of the trial centres. Correct position of the port catheter will be checked again through X-ray or fluoroscopy (tip of the catheter in the superior vena cava just at the level of bronchial bifurcation). Flow for blood withdrawal and infusion will be tested via cutaneous puncture (Huber needle). To complete the procedure the system will be blocked by means of saline, with or without heparin, according to local standards.

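### The skin-to-suture duration starts at different events in the two arms, so part of any between-arm difference in it comes from the definition and from the guidance mix

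*Protocol article*

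**What the plan says.** The section on duration of the port implantation procedure, under secondary endpoints, defines two measures.

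- The first is a procedure interval. In the open arm it is worded, "For the open strategy, the time from cutaneous incision to last knot of intracutaneous suture". In the closed arm it is "the time from first intervention on the patient (that is, first sonography, first radiography or first puncture) to the last knot" of the same kind of suture.
- The second is worded identically for both arms: "the time from the patient entering the intervention room until the patient has left, will be measured".

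Both are entered in the CRF on the day of intervention, and neither is given priority.

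The treatment descriptions fix where anaesthesia falls. Open strategy: "Following the infiltration of local anaesthesia in sterile fashion into the skin and subcutaneous layer, a cutaneous incision will be made". Closed strategy: the article first describes guidance by sonography, fluoroscopy (with a contrast check of the vein) or landmarks, and then states: "Local anaesthesia will be infiltrated in sterile fashion into the skin and periosteum of the clavicle". Marking of the site, an optional skin incision and the puncture follow.

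Under further analyses, secondary variables are summarised by arm, with descriptive P values and 95% confidence intervals for the group comparison.

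**The concern.** An operating-time comparison is interpretable only if the clock means the same thing in both arms. Here the open-arm clock leaves out an invasive preparatory step, anaesthetic infiltration, while the closed-arm clock can start at a non-invasive one, a sonographic scan, and then run through infiltration. Randomisation balances patients, but it does not remove a difference built into how the outcome is measured. A larger sample only estimates that difference more precisely.

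The closed-arm start also depends on the guidance method, which the article leaves to the centre. The built-in offset is therefore not a constant that could be subtracted afterwards. What is at stake is the reading of one secondary endpoint: a difference in procedure time could be reported as a property of the strategy when part of it comes from the clock.

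**Working it through.** **Step 1. The definitions against the order of steps.**

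| Arm and guidance | Clock starts at | Guidance imaging counted? | Local anaesthesia counted? |
|---|---|---|---|
| Open | Skin incision | Not applicable at the start | No, it comes before the incision |
| Closed, imaging before anaesthesia | First sonography or radiography | Yes | Yes |
| Closed, imaging only after anaesthesia | First imaging or puncture | From that point on | No |
| Closed, landmark | First puncture | None | No; an optional skin incision also falls before the start |

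The article describes guidance before anaesthesia, but for sonography it says only that a device may be used to visualise the vein. It does not fix the order. The second and third rows are therefore both possible.

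**Step 2. What the comparison estimates.** Let *f* be the share of closed-arm patients whose clock starts with imaging before anaesthesia, *d* their mean offset against the open-arm clock, and *e* the mean offset in the rest (near zero or negative). Then

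observed difference = true difference + *f* × *d* + (1 − *f*) × *e*.

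The article gives none of *f*, *d* or *e*, and no mean or SD for duration. The offset cannot be computed from it.

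**Step 3. The group size used below.** The article states no figure for duration. Its 577 per group is for the primary endpoint (3% against 0.5%, two-sided 5%, power 0.9), and it reproduces:

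n = [1.960 × √(2 × 0.0175 × 0.9825) + 1.2816 × √(0.03 × 0.97 + 0.005 × 0.995)]² / 0.025² = (0.3635 + 0.2366)² / 0.000625 ≈ 576.04, rounded up to 577.

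**Step 4. Illustration with assumed SDs and offsets.** Take 577 per arm and no true difference. The standard error is SD × √(2/577), and the chance of P<0.05 is approximately Φ(offset/SE − 1.96).

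| Assumed SD (min) | SE (min) | Average offset 2 min | Average offset 5 min |
|---|---|---|---|
| 10 | 0.59 | 0.925 | 1.000 |
| 15 | 0.88 | 0.620 | 1.000 |
| 20 | 1.18 | 0.397 | 0.989 |
| 25 | 1.47 | 0.274 | 0.925 |

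Worked case, SD 25 and offset 2: SE = 25 × √(2/577) = 1.47; 2/1.47 = 1.36; Φ(1.36 − 1.96) ≈ 0.27.

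These offsets are averages over the whole closed arm. Landmark patients pull the average down, so the offset among image-guided patients would have to be larger to produce the same result.

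**The case against.** A reader might infer that the definition always lengthens the closed strategy, or that a shorter open-arm time would simply be an artefact. The article supports neither. With landmark guidance the closed clock starts at puncture, after anaesthesia and possibly after a skin incision, so the offset can vanish or favour the closed arm.

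Nor is all counted imaging error. This is a pragmatic comparison of strategies, and guidance imaging is work that the closed strategy brings with it. It may fairly be counted. The clearly non-comparable part is local anaesthesia, which is never counted in the open arm and sometimes counted in the closed arm.

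The stop event might also look faulty, because it refers to an intracutaneous suture while the article says: "Wound closure will be performed in accordance with the local standards of the trial centres". That sentence appears for both strategies, and randomisation is stratified by centre, so it creates no systematic difference between arms. It is a wording matter only.

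The strongest objection is that a symmetric measure, room entry to room exit, is already collected, that duration is secondary, and that its P values are descriptive. This limits the consequence but does not make the first interval comparable. The article sets the two measures side by side, gives no reason for the unequal start, and plans a group comparison of secondary variables without excepting this interval.

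**Conclusion.** The point stands as a definitional mismatch in one of two duration measures. The between-arm difference in the procedure interval depends partly on where the clock starts and on the guidance mix.

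Its direction is not fixed. It lengthens the closed arm where imaging starts the clock before anaesthesia, and it may be near zero or reversed under landmark guidance. Its size is unknown. The range of about 27% to 93% for a 2-minute average offset rests wholly on assumed SDs of 25 to 10 minutes. It shows only that at this sample size a small built-in offset can be enough to produce a nominally significant result.

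The primary endpoint, its test and the sample size are unaffected. This is a modest point, worth correcting because the remedy is cheap.

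**What to change.** - Make room-entry to room-exit time the between-arm comparison of duration. This also covers patients already recorded; the article reports that recruitment began in November 2014.
- Report the current procedure interval within arm only, without a between-arm P value or confidence interval.
- For future patients, use one start rule in both arms: the earlier of first guidance imaging or local anaesthetic infiltration. Starting at infiltration alone would drop imaging done before it and so favour the closed arm.
- Use one stop in both arms, the end of skin closure, which does not depend on the closure method.

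The cost is a small change to the CRF and the analysis text, with no change to treatment. Room time is already collected. The downside is that room time is likely to be more variable than the procedure interval, so the comparison will be less precise.

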##### Subjective tolerability of intervention

This is defined as a subjective rating of the tolerability of the intervention by the patient. It will be assessed on the day of operation, after the intervention has taken place*.* Patients will be asked two questions rating the tolerability of the intervention on a standardised Likert scale (1 = well tolerable to 5 = intolerable). Furthermore, the willingness of the patients to repeat the intervention under the same conditions will be assessed. The answers will be documented in the CRF.

##### Primary success rate

Primary success is defined as correct positioning of the tip of the catheter in the superior vena cava with the randomised strategy at the intended side, controlled intra- or post-operatively by radiography, and correct function of the catheter, checked by blood sampling and infusion of fluid. Primary success will be assessed post-operatively by the responsible physician and documented in the CRF. A copy of the intra-operative radiograph showing the catheter in the correct position will be saved in digital form using radiological image viewing software (for example, Centricity), or a copy of the original radiograph will be archived.

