**Methods/Design:**

The PORTAS-3 trial is designed as a multicentre, randomised controlled trial to compare two implantation strategies. A total of 1,154 patients will be randomised after giving written informed consent. Patients must be over 18 years of age and scheduled for primary implantation of a TIVAP on the designated side. The primary endpoint will be the frequency of pneumothorax and haemothorax after insertion of a TIVAP by one of two different strategies. The experimental intervention is as follows: open strategy, defined as surgical cut-down of the cephalic vein, supported by a rescue technique if necessary, and in the case of failure, direct puncture of the subclavian vein. The control intervention is as follows: direct puncture of the subclavian vein using the Seldinger technique guided by sonography, fluoroscopy or landmark technique. The trial duration is approximately 36 months, with a recruitment period of 18 months and a follow-up period of 30 days.

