## Background

Totally implantable venous access port (TIVAP) implantation was first introduced in the early 1980s by Niederhuber *et al*. [1]. Following further refinement, the technique has been adopted worldwide to create a safe and permanent venous access for chemotherapy (CHT) and/or parenteral nutrition. TIVAPs last longer, have lower infection rates and are more suitable for active patients than external central venous catheters (such as the Hickman´s catheter) [2]. The number of TIVAP insertions is constantly increasing. In Germany, 480,176 new cases of oncological diseases were diagnosed in 2010. In 2008, 80,034 TIVAP implantations were performed on in-patients in German hospitals, and it is estimated that more than 101,000 TIVAP implantations were performed in an out-patient setting in 2012 [3].

The techniques most often used for insertion of TIVAPs are surgical cut-down of the cephalic vein ((SCD) open strategy), accomplished predominantly by surgeons, and puncture of the subclavian vein ((PSV) closed strategy), performed by surgeons or interventional radiologists. The median primary success rates given in various retrospective studies and a small number of single-centre, randomised controlled trials range from 71 to 94% for SCD, and from 90 to 99% for PSV [2,4-13]. Common complications, such as kinking or dislocation of the catheter, subcutaneous haematoma, wound infection and nerve palsy, are observed with both techniques; however, specific risks are associated only with PSV, including the ‘pinch-off’ phenomenon, pneumothorax and haemothorax, which in most cases requires further treatment and often admission to hospital [14-16]. In the literature, the rate of pneumothorax and haemothorax after PSV is reported to be about 3%, ranging up to 6% in prospective studies [14-18]. In contrast, if SCD is successful there is no risk for pneumothorax or haemothorax; however, in some cases implantation via SCD is not possible, so PSV is required to implant the TIVAP. If SCD fails, a rescue technique (RT) can be executed using a guide wire, vein dilator and peel-away sheath through the cephalic vein to overcome narrow vessels or obstructions, thus avoiding PSV and its subsequent risks. Although TIVAP implantation is one of the top 50 (surgical) interventions in Germany, no multicentre trial comparing these two strategies has been performed.

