## Methods/Design

### Aim of the trial

The PORTAS-3 trial, a multicenter, randomized, controlled trial comparing complication rates of open and closed implantation strategies for insertion of a totally implantable venous access port (TIVAP) in oncological patients, is a pragmatic trial that aims at comparing the open strategy (SCD and if necessary RT; if both fail, PSV) to the closed strategy (PSV) with regard to the frequency of pneumothorax and haemothorax.

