### Sample size

A review of the previous literature, including our own randomised controlled trials, revealed a pneumothorax and haemothorax rate of about 3% for placement of a TIVAP by PSV; however, there is no risk if implantation by SCD is successful [14-18]. SCD was successful in 71 to 94% of cases (including the RT), therefore, about 17.5% of patients underwent PSV as a secondary implantation technique. Thus, the overall risk of pneumothorax and haemothorax for the open strategy is about 0.5% (0.175 × 0.03). Assuming a difference of 2.5%, a trial with a desired power of 0.9 and a type 1 error of 0.05 would need to include 577 patients per group to detect this difference in pneumothorax and haemothorax frequency when applying a chi-square test. No missing values for the primary endpoint are assumed, so a total of 1,154 patients have to be randomised into the two intervention groups. A Consolidated Standards of Reporting Trials (CONSORT) flow chart is provided in Figure 1.

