## Discussion

TIVAP implantation is one of the most common general surgical procedures [3] and is performed routinely by either SCD or PSV. However, only few randomised controlled trials [4,6,9,17] and no multicentre trials compared these techniques for their potential risks and benefits. The aim of the PORTAS-3 trial is to compare a primary open strategy (SCD with RT if necessary; PSV if the aforementioned fail) to a primary closed strategy (PSV; SCD if PSV fails) in regard to the frequency of post-operative pneumothorax and haemothorax, with the hypothesis that the open strategy is able to significantly reduce the risk of pneumothorax and haemothorax occurrence.

The PORTAS-3 trial is designed as a pragmatic trial, since the objective is to depict the real medical treatment situation. Therefore, just some key steps of the interventions are predefined, and the rest can be performed according to local practice of the centres. For instance, in PSV either sonography, fluoroscopy or anatomical landmarks can be used for guidance of the puncture. Some authors suggested that sonographic guidance should be the method of choice for vascular cannulation due to improved safety [26]. Even though ultrasound is widely available nowadays, this still does not represent comprehensive clinical practice in a lot of hospitals, and a recent Cochrane review on ultrasound guidance for subclavian vein catheterization [27] could only show a reduced risk of arterial cannulation, and no reduction for other complications like pneumothorax and haemothorax.

The results of the PORTAS-3 trial will be applicable to a wide range of patients and could influence future guidelines and decision-making. Healthcare costs might be reduced by the reduction of complications and necessary treatment and hospitalization for these complications. Furthermore, required treatment of patients (for example, with CHT) will not be delayed by potential complications.

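### Primary success is tied to the randomised strategy, so the wording allows a failed cut-down rescued by puncture to count as a primary success, and it asks for a radiographic check that group A does not always require

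*Protocol article*

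**What the plan says.** - **Definition.** Under Secondary endpoints, Primary success rate, the article requires "correct positioning of the tip of the catheter in the superior vena cava with the randomised strategy at the intended side", controlled during or after the operation by radiography, together with correct function on blood sampling and infusion. The responsible physician assesses it.
- **Open strategy.** The Abstract describes cut-down "supported by a rescue technique if necessary, and in the case of failure, direct puncture of the subclavian vein". The Aim of the trial agrees: "the open strategy (SCD and if necessary RT; if both fail, PSV").
- **Closed strategy.** The Abstract and the aim give PSV with no fall-back: "comparing the open strategy (SCD and if necessary RT; if both fail, PSV) to the closed strategy (PSV"). The Discussion gives it one: "to a primary closed strategy (PSV; SCD if PSV fails").
- **Use of the term elsewhere.** The Background reports primary success rates by single technique; they "range from 71 to 94% for SCD, and from 90 to 99% for PSV". The Sample size section says "SCD was successful in 71 to 94% of cases (including the RT") and treats PSV after a failed cut-down as a second-line technique, expected in about 17.5% of patients.
- **Position checks.** In group A the tip is checked by X-ray, by fluoroscopy (tip "at the level of bronchial bifurcation) or intraatrial electrocardiogram"). In group B the same three options apply at insertion, but the position is then checked again by X-ray or fluoroscopy.
- **Analysis.** Secondary variables are summarised descriptively, with descriptive P values and 95% confidence intervals (Further analyses).

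**The concern.** The word strategy decides who counts as a success. Because the open strategy contains its own fall-back, a patient whose cut-down and rescue technique both failed, and who then had a successful PSV on the intended side, meets the definition. Nothing in the article says that conversion is a primary failure. The Background's success rates, which a reader would naturally set beside the result, are by technique and so measure something else.

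The closed arm is uncertain too: whether a failed PSV followed by cut-down counts depends on which description of the closed strategy applies. Unblinded physicians at several centres make the assessment, so conversions may also be coded differently between centres.

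The second problem is independent of the first. The definition demands radiographic control, yet group A may rely on intra-atrial ECG alone. A correctly placed, working catheter checked only by ECG does not meet the definition. This cannot arise in group B if its procedure is followed.

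At stake is a between-arm contrast, reported with a P value and interval, whose sign depends on how one word is read.

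**Working it through.** **The plan's own figures first.** The 17.5% is one minus the midpoint of 71% and 94%: 1 - 0.825 = 0.175. The 577 per group reproduces for 3% versus 0.5%, two-sided alpha 0.05, power 0.90, chi-square test without continuity correction:

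n = [1.960 x sqrt(2 x 0.0175 x 0.9825) + 1.2816 x sqrt(0.03 x 0.97 + 0.005 x 0.995)]^2 / 0.025^2 = 576.04, rounded up to 577.

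Here 577 serves only as the arm size.

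**Inputs.** s = success of SCD including the rescue technique, 71 to 94%, midpoint 82.5% (Sample size). p = success of PSV, 90 to 99%, midpoint 94.5% (Background).

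**Assumptions, not in the documents.** A technique used as fall-back succeeds as often as when used first; the fall-back is on the intended side; every success is verified radiographically.

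**Patients affected.** Conversions in the open arm: 577 x 0.175 = 101. Of these, 577 x 0.175 x 0.90 = 91 to 577 x 0.175 x 0.99 = 100 would count as primary successes. Over the full ranges: 577 x 0.06 x 0.90 = 31 to 577 x 0.29 x 0.99 = 166.

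**Three readings at the midpoints.**

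| Reading | Open | Closed | Open minus closed (95% CI at 577 per arm) |
|---|---|---|---|
| First technique: s vs p | 82.5% | 94.5% | -12.0 points (-15.6 to -8.4) |
| Literal, closed = PSV only: s + (1-s)p vs p | 0.825 + 0.175 x 0.945 = 99.0% | 94.5% | +4.5 points (+2.5 to +6.6) |
| Literal, closed = PSV then SCD: s + (1-s)p vs p + (1-p)s | 99.0% | 0.945 + 0.055 x 0.825 = 99.0% | 0 |

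In the third row both arms equal 1 - (1-s)(1-p), so the expected difference is zero whatever s and p are.

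**Over the ranges** (s = 71, 82.5, 94%; p = 90, 94.5, 99%). By first technique the difference runs from -28.0 to +4.0 points and is negative in 8 of 9 combinations; the exception is s = 94%, p = 90%. On the literal reading with closed = PSV only it runs from +0.7 to +9.4 points and is positive in all 9. The sign of the expected difference therefore changes in 8 of 9. In some of these, one of the two intervals includes zero (for example the literal reading at s = 82.5%, p = 99%: +0.8 points, -0.1 to +1.7).

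**Sensitivity to fall-back success r.** On the literal reading with closed = PSV only, the open arm is ahead when s + (1-s)r > p. At the midpoints: r > (0.945 - 0.825) / 0.175 = 0.69.

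**Radiographic requirement.** The share of ECG-only checks is not given. At the midpoints the literal advantage of 4.54 points equals 0.0454 x 577, about 26 patients. If about 26 successful cut-downs, of 0.825 x 577 = 476, had only an ECG check, that advantage would be gone.

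**The case against.** The strongest reply is that the authors meant the first technique. The Background loosely labels cut-down as the open strategy and puncture as the closed one, and uses primary success for each technique; the Sample size section treats the fall-back puncture as second-line. On that usage, primary success with the randomised strategy means success without conversion. This stands as a possible reading, and it is why the fault is a wording that supports two results rather than one that is plainly wrong. The definition does not state that reading, and the Abstract and aim define the strategy otherwise.

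A second reply is that strategy-level success is a legitimate measure in a pragmatic comparison of strategies. That is true, and it deserves its own line in the results; it is not what the Background calls primary success.

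A reader might also infer that the trial would hide the conversion rate. The documents do not support that. Skill of surgeons provides for recording complex or unsuccessful primary implantations, and Visit two records the intervention performed and the procedure as executed. First-technique success and conversion can be derived in each arm.

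On radiography, the definition accepts intra-operative images, and its section provides for archiving one, so the mismatch concerns only cases checked by ECG alone. The selective chest X-ray under Primary endpoint serves to detect pneumothorax and haemothorax and is not evidence about tip control.

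**Conclusion.** The concern holds as an ambiguity with a material effect on one secondary endpoint. The same data at the midpoints would be expected to give about -12, +4.5 or 0 points, depending on the meaning of strategy and on which description of the closed strategy applies. This rests on equal fall-back and first-line success, and on full radiographic verification.

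A reader might conclude that the comparison simply reverses in favour of the open arm, with near-complete success reported there. The documents do not support that as a general statement. The reversal needs closed to mean PSV only; under the Discussion's description the difference is zero. It also depends on fall-back success, and ECG-only cases would pull open-arm success down by an amount that cannot be estimated. The two faults push in opposite directions and their net effect is unknown.

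The endpoint is secondary and descriptive. The primary endpoint, its test and the sample size are untouched. It should be corrected, but it does not threaten the trial's main conclusion.

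**What to change.** 1. Define primary success as correct tip position and function, on the intended side, with the arm's first-line technique (SCD with or without the rescue technique; PSV), without conversion. Count conversion in either arm as a primary failure.
2. Report overall success after any conversion as a separate descriptive result.
3. Make the position check in the definition match the checks that the group A and group B sections permit, identically in both arms.
4. Reconcile the closed strategy in the Abstract and aim with the one in the Discussion. Which is intended is for the trial team to state.

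The cost is wording, plus a short note to centres because recruitment has begun. No new data are needed: the fields described under Skill of surgeons and Visit two allow the endpoint to be derived centrally, including for patients already enrolled, and ECG-only cases need no extra imaging.
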